## Abstract

**Introduction:**

Rheumatoid arthritis (RA) is a chronic inflammatory autoimmune disease that may lead to bone erosion and disability. Although there are many biological therapies in RA treatment nowadays, such as etanercept and tofacitinib, there are still a considerable number of patients who cannot achieve clinical deep remission, which makes patients feel pain and stiffness of joints. As a traditional Chinese medicine preparation, Wangbi granule showed a synergistic role with methotrexate in the treatment of RA patients with “kidney deficiency and dampness” or “stasis blocking channels”. Therefore, it is a promising therapeutic strategy for the clinical deep remission of RA. In this study, Wangbi granule will be used as the test drug. The investigators conduct this study to evaluate the efficacy and safety of Wangbi granule in the treatment of patients who have not achieved deep remission despite the use of methotrexate and tofacitinib.

**Methods and analysis:**

Two parallel randomized, triple-blind, placebo-controlled trials will be conducted. In six study centers, 340 eligible RA patients will be recruited and randomly allocated to either the intervention group or the control group (in a 1:1 ratio). They will receive Wangbi granule or Wangbi placebo 12.0 g each time, three times a day for 12 weeks. The primary outcome is the disease activity score derivative for 28 joints (DAS28). Secondary outcomes are patient-reported outcomes, American College of Rheumatology 50% response criteria (ACR50), fatigue scale-14 (FS-14), visual analogue scale for pain (VAS), health assessment questionnaire disability index (HAQ-DI) and biomarkers such as C-reactive protein (CRP) and erythrocyte sedimentation rate (ESR).

**Expected outcomes:**

The success of this study will provide strong evidence to confirm the efficacy and safety of Wangbi granule in the treatment of RA.

*Trial registration* The trial has been registered in the ClinicalTrials Registry (NCT05540938, Date: 09/15/2022, https://clinicaltrials.gov/ct2/show/NCT05540938)

## Background

Rheumatoid arthritis (RA) is a chronic inflammatory autoimmune disease and is currently one of the major disabling diseases worldwide, with a prevalence of about 1% [1, 2]. RA is mainly manifested as chronic synovial inflammation, which undergoes synovial proliferation, infiltration of immune and inflammatory cells, and eventually progresses to destruction of cartilage and bone, resulting in limited joint movement and physical disability [3]. Disease activity and bone erosion in RA have been the most important clinical concerns. Reducing disease activity, controlling synovial inflammation, and delaying bone destruction are the crucial issues that need to be addressed.

The standard of care for RA has gone through phases of hormones, non-steroidal antiinflammatory drugs (NSAIDs), conventional synthetic disease-modifying antirheumatic drugs (csDMARDs), biologic disease-modifying antirheumatic drugs (bDMARDs) and target-mediated drug for small molecules [4]. The prognosis of RA has been improved substantially due to the appearance of bDMARDs and target-mediated drug for small molecules. However, once RA is controlled, dose reduction or withdrawal of these drugs must be taken into consideration because of infection risk, dose-dependent adverse events, or treatment cost. More importantly, during the treatment process, even after intensive Western medication, there are a considerable number of patients who cannot achieve clinical deep remission, which makes patients still feel pain and stiffness of joints [5], and gradually lead to a series of complications such as chronic fatigue and diffuse pain [6, 7]. In the case of the methotrexate combined with tofacitinib regimen, for example, a study demonstrated that even with the application of this more therapeutically potent intervention, only 46% of patients could achieve an American College of Rheumatology 50% response criteria (ACR50) after 6 months of treatment, and 7% of patients experienced adverse events [8]. Therefore, finding new treatment options to achieve deep remission in RA patients, and relieve chronic fatigue and diffuse pain based on current treatment is an urgent issue for clinicians to address.

Chinese medicine is effective in the treatment of RA, with relatively mild side effects and suitable for long-term use [9]. The Wangbi granule, a well-known Chinese patent medicine, was developed by Liaoning Good Nurse Pharmaceutical (Group) Co., Ltd. (Benxi City, Liaoning Province, China) and approved by the China Food and Drug Administration (No: Liao20150121) for the treatment of RA [10]. The latest research has shown that Wangbi granule has impressive anti-inflammatory and immunomodulatory effects and can reduce pathological hyperplasia and bone destruction in damaged joints [11, 12]. As a traditional Chinese medicine preparation, Wangbi granule showed a synergistic role with methotrexate in the clinical treatment of early RA, contributing to the remission of RA [13]. However, stronger evidence is needed to confirm its further therapeutic effects in RA that has been treated but not yet reached a complete remission. This will help clinicians to better manage the course of RA patients.

In conclusion, the investigators will conduct this randomized controlled trial to evaluate the efficacy and safety of Wangbi granule in RA patients who did not achieve deep remission despite treatment with tofacitinib and methotrexate.

## Methods

### Study design

The clinical study of Wangbi granule for RA is a multicenter, randomised, triple-blind, placebo-controlled superiority trial. The study flow is designed strictly according to the CONSORT Statement and SPIRIT Statement [14, 15] (Fig. 1). The study will restrict the enrollment of participants, use strict randomization and blinding, and apply some statistical methods to prevent possible bias in these ways.

**Fig. 1 Fig1:**
[figure not shown]
The flow diagram of the trial. T0, 0–1 day treatment (baseline); T1, 4 week treatment; T2, 8 week treatment; T3, 12 week treatment; T4, 1 month after end of treatment; *DAS28* disease activity score derivative for 28 joints, *ACR50* American College of Rheumatology 50% response criteria, *VAS* visual analogue scale for pain, *FS-14* fatigue scale-14, *HAQ-DI* health assessment questionnaire disability index, *ALT* alanine aminotransferase, *AST* aspartate aminotransferase, *Scr* serum creatinine, *ESR* erythrocyte sedimentation rate, *CRP* C-reactive protein, *RF* rheumatoid factors, *ACPA* anti-citrullinated protein antibodies

### Eligibility criteria

Patients aged 18–75 years who meet the 1987 or 2010 international diagnostic criteria for RA are eligible for the study [16, 17]. Patients need to meet the diagnostic criteria (2018 edition) for “kidney deficiency and dampness” and “stasis blocking channels” in Chinese medicine [18]. The disease activity score derivative for 28 joints (DAS28) [19] score should be 2.6 to 3.2. The use of methotrexate (7.5–15 mg, quaque week, dose changes with disease) in combination with tofacitinib (5 mg, bis in die) for more than 12 weeks prior to recruitment is required. Before recruitment, clear notification and signing of informed consent are required.

Exclusion criteria include: taking immunosuppressants other than methotrexate and tofacitinib in the 3 months prior to recruitment; combination of other severe multi-system damaging diseases; presence of cognitive impairment, psychosomatic disorders, peripheral neurological disorders; those who are pregnant, breastfeeding, or have a planned pregnancy; overweight, allergic to the study drug, or enrolled in another clinical trial; other conditions in which the investigator believes the patient should not participate in the trial. The complete list of inclusion and exclusion criteria is provided in Table 1.

**Table 1 Tab1:** Inclusion and exclusion criteria of the trial

Inclusion criteria	Exclusion criteria
► Age 18–75 years ► Meeting the 1987 ACR or 2010 ACR/EULAR diagnostic criteria ► Meeting the diagnostic criteria for “kidney deficiency and dampness” and “stasis blocking channels” in Chinese medicine ► DAS28 score of 2.6 to 3.2 ► Regularly taking methotrexate (7.5–15 mg qw) and tofacitinib (5 mg bid) before enrollment and stable treatment regimen for more than 12 weeks ► Voluntary participation and signed written informed consent	► Patients taking immunosuppressive drugs other than methotrexate and tofacitinib within 3 months prior to enrollment ► Organ transplant recipients, patients with malignant tumors, patients with heart, brain, liver (ALT/AST > 3 times the normal upper limit), kidney (Ccr < 60 ml/min) and other important organ function impairment or hematological system diseases ► Psychiatric disorders such as cognitive disorders, depression, anxiety disorders, somatic dysfunction, cerebral infarction, cerebral hemorrhage, epilepsy, TIA, myelitis, demyelinating lesions and other central neurological disorders, or peripheral neurological disorders such as restless legs syndrome. peripheral neurological disorders such as restless legs syndrome ► Women and men who are pregnant or breastfeeding or who are planning a pregnancy within the next 6 months; during the trial or within 1 month of the last dose Women of childbearing age who are unable or unwilling to use adequate contraception, or whose spouse is unwilling to use contraception, within 1 month of the last dose or within 1 month of the last dose are unwilling to use contraception ► Persons with a BMI greater than 35 (kg/m^2^), allergic to the test drug, or participating in other clinical trials ► Other conditions deemed by the investigator to be inappropriate for trial participation (out-of-town patients unable to be followed up, etc.)

*ACR* American college of rheumatology, *EULAR* European league against rheumatism, *DAS28* disease activity score derivative for 28 joints, *qw* quaque week, *bid* bis in die, *DMARDs* disease-modifying antirheumatic drug, *ALT* alanine aminotransferase, *AST* aspartate aminotransferase, *Ccr* creatinine clearance rate, *TIA* transient ischemic attacks, *BMI* body mass index

Participants may decide to withdraw from the trial at any time for any reason of their own choosing. The investigators may also ask the participant to withdraw from the trial for rational reasons. All participants who have completed the informed consent form and are screened and qualified to enter the randomized trial, regardless of when and why they withdrew, will be treated as dislodged cases as long as they do not complete the observation period specified in the protocol.

### Study setting

This trial is led by the Traditional Chinese Medicine Department of Rheumatology at China-Japan Friendship Hospital and will be conducted at 6 hospitals in China (China-Japan Friendship Hospital, Peking Union Medical College Hospital, The First Affiliated Hospital of Anhui University of Traditional Chinese Medicine, The 980th Hospital of PLA Joint Logistics Support Force, The Second Affiliated Hospital of Zhejiang Chinese Medical University, and The First Hospital Affiliated to Army Medical University).

### Recruitment

A total of 340 patients will be recruited from the 6 centers participating in this study. An investigator, assisted by a trained study coordinator at each participating center, will identify potential eligible patients based on the eligibility criteria. They will work with the attending physician to determine whether the patient is eligible for the trial. Patients who travel to outpatient or inpatient settings for RA are evaluated for eligibility by an investigator who collects relevant information face-to-face with the patient’s verbal consent at the time of treatment. If RA patients are recruited from posters, the internet, etc., eligibility will be assessed over the phone. After the patient is deemed to meet the criteria for participation, the investigator will inform the study protocol in detail, at which point potential participants can ask their questions and requests, and after formally signing written informed consent, they are enrolled in the trial as participants.

### Interventions

After being recruited, patients will be randomly allocated to either the intervention group or the control group (in a 1:1 ratio).

Based on the treatment of methotrexate (7.5–15 mg, quaque week, dose changes with disease) (Shanghai Sine Pharmaceutical, Shanghai, China) and tofacitinib (5 mg, bis in die) (Qilu Pharmaceutical, Shandong, China), patients in the intervention group will be given Wangbi granule (12 g, ter in die) (Good Nurse Pharmaceutical, Liaoning, China) and patients in the control group will be given Wangbi placebo (12 g, ter in die) (Good Nurse Pharmaceutical, Liaoning, China). To reduce the adverse effects of methotrexate, folic acid (10 mg, quaque week) (Lisheng Pharmaceutical, Tianjin, China) will be used in combination with all treatments.

All the botanical or zoological drugs that make up the Wangbi granule are explained in Table 2. All trial drugs will be manufactured and supplied by Liaoning Good Nurse Pharmaceutical (Group) Co., Ltd. (Benxi City, Liaoning Province, China) and tested by its quality management department to meet the Pharmacopoeia of China (2020 edition) grade standards. Voucher samples of all drugs will be stored at China-Japan Friendship Hospital (Beijing, China). The drug preparation and packaging will be operated by the pharmacy of Good Nurse Pharmaceutical in a fully enclosed production line. All ingredients will be mixed in the original dosage, steeped in pure water for 0.5 h, heated to boiling, decocted for 2 h, filtered from the aqueous extract, then the residue will be added to pure water and decocted for 1 h. The two liquid extracts will be combined, settled, filtered and concentrated into a thick paste (relative density 1.32–1.35, 50 °C), with a certain amount of soluble starch and dextrin as auxiliary materials to assist in forming, and processed into 1000 g concentrated granules by spray drying. The final Wangbi granule is equivalent to 27.88 g of the original drugs per 12 g (ter in die, a total of about 83.63 g per day) and sealed with aluminum-plastic composite film (BOPP/AL/CPE) packaging material. The Wangbi granule needs to be dissolved in hot water for each use. The placebo consists of one tenth of the dosage of Wangbi granule, starch, caramel color and bitter agent. Its appearance and odor are the same as those of Wangbi granule. The study drugs are from the same batch, purchased from Good Nurse Pharmaceutical (Liaoning, China), coded and kept under lock and key by the drug administrator in a special cabinet at room temperature and dry place. On the day of enrollment, patients will be given these medications.

**Table 2 Tab2:** Components of Wangbi granule (intervention drug)

Chinese name	Chinese Pinyin	Scientific name	Family	Part used	Original dosage (g)	Daily dosage(g)
生地黄	Sheng Di Huang	*Rehmannia glutinosa* (Gaertn.) DC.	Orobanchaceae	Dried root	196	7.056
熟地黄	Shu Di Huang	*Rehmannia glutinosa* (Gaertn.) DC.	Orobanchaceae	Steamed root	196	7.056
续断	Xu Duan	*Dipsacus asper* Wall. ex DC.	Caprifoliaceae	Dried root	147	5.292
附子	Fu Zi	*Aconitum carmichaeli* Debeaux	Ranunculaceae	Dried lateral root tuber	147	5.292
独活	Du Huo	*Angelica biserrata* (R.H.Shan & C.Q.Yuan) C.Q.Yuan & R.H.Shan	Apiaceae	Dried root	98	3.528
骨碎补	Gu Suibu	*Drynaria roosii* Nakaike	Polypodiaceae	Dried rhizome	147	5.292
桂枝	Gui Zhi	*Neolitsea cassia* (L.) Kosterm.	Lauraceae	Dried young branch	98	3.528
淫羊藿	Yin Yanghuo	*Epimedium sagittatum* (Siebold & Zucc.) Maxim.	Berberidaceae	Dried aerial parts	147	5.292
防风	Fang Feng	*Saposhnikovia divaricata* (Turcz. ex Ledeb.) Schischk.	Apiaceae	Dried root	98	3.528
威灵仙	Wei Lingxian	*Clematis chinensis* Osbeck	Ranunculaceae	Dried root and rhizome	147	5.292
白芍	Bai Shao	*Paeonia lactiflora* Pall.	Paeoniaceae	Dried root	117.67	4.236
狗脊	Gou Ji	*Cibotium barometz* (L.) J.Sm.	Cyatheaceae	Dried rhizome	147	5.292
皂角刺	Zao Jiao Ci	*Gleditsia sinensis* Lam.	Fabaceae	Dried spine	98	3.528
知母	Zhi Mu	*Anemarrhena asphodeloides* Bunge	Asparagaceae	Dried rhizome	147	5.292
伸筋草	Shen Jincao	*Lycopodium japonicum* Thunb.	Lycopodiaceae	Dried herb	98	3.528
红花	Hong Hua	*Carthamus tinctorius* L.	Asteraceae	Dried flower	98	3.528
羊骨	Yang Gu	*Capra hircus* L.	Caprinae	Dried bone	196.44	7.072

Except for the experimental drugs, the participants are not allowed to use other botanical, zoological and Western medicines with immunosuppressive or immunomodulatory effects. All treatments that may improve RA, such as acupuncture and massage, will be banned during the trial. If a patient has special circumstances during the observation period, for instance. In that case, when pain is unbearable, drugs such as low-dose NSAIDs can be used in combination under the direction of the investigator, and all drug use outside the study protocol must be recorded in detail.

The participants will take the drugs daily for 12 consecutive weeks under self-monitoring. During the course of the medication intervention, we will strictly ensure that participants are adequately adherent. After the participant has formally decided to participate in the clinical study, the investigator will explain the entire trial process, including the time points at which various types of information will be collected, the meaning of every terminology in the questionnaire, the frequency and method of how participants need to take drugs. Participants are required to fill out daily health monitoring forms to record medication intake and changes in the condition so that the investigator can check. Participants will be asked to bring all leftover drugs to every follow-up visit to check their compliance. Investigator faithfully recorded the number of drugs received, taken and returned by the participant and promptly recorded them on the case report form. Once a participant enrolled in the study, the drugs used and the tests involved will be covered by the study center and the participant will be reimbursed a certain amount of grants when the trial is completed in full. Through these incentives, participants will maximize their enthusiasm for the trial, which is expected to improve in RA clinical conditions.

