### Sample size calculation

The study used superiority design approach. Due to the lack of clinical studies of methotrexate and tofacitinib in combination with Wangbi granule, we refer to the previous studies of methotrexate in combination with Wangbi granule for the treatment of RA [25]. In order to observe the deep remission effect of the Wangbi granule on RA condition, the final DAS28 score of the intervention group needs to be at least 0.5 points lower than that of the control group, so the cut-off value δ takes − 0.5. We adopted single-sided calculation whereα is 0.025, β is 0.2, and the sample size is 1:1, then the single group sample size of 155 cases is obtained. Considering a shedding rate of 10%, 170 cases are needed in each group, and the final total sample size is 340.According to the plan, as the lead center, China-Japan Friendship Hospital will complete the intake of 90 samples, and the remaining 5 centers will equally distribute the remaining 250 samples.

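### The control preparation carries one tenth of the Wangbi dose, so the trial compares full with one-tenth dose, but its placebo wording, efficacy and safety conclusions and limitations do not say so

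*Protocol article*

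**What the plan says.** All references are to the protocol article.

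- **Interventions**, on the control preparation: "The placebo consists of one tenth of the dosage of Wangbi granule, starch, caramel color and bitter agent". Both arms take 12 g three times daily, for 12 consecutive weeks, on top of methotrexate and tofacitinib. Matching appearance and odour are described in the same paragraph.
- **Study design** calls the study a "randomised, triple-blind, placebo-controlled superiority trial". The Abstract and the Conclusion use the same label, and Statistical analysis names the comparison as granule against placebo.
- **Abstract, Expected outcomes** looks forward to firm evidence on both the efficacy and the safety of the product. It does not qualify what the comparison was made against.
- **Discussion** lists two limitations: subjective scoring and short follow-up. The control's active content is not among them.
- **Sample size calculation** requires that "the final DAS28 score of the intervention group needs to be at least 0.5 points lower than that of the control group". On the background for this it says "we refer to the previous studies of methotrexate in combination with Wangbi granule for the treatment of RA", without describing what those studies compared Wangbi with.

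**The concern.** A reader who sees a placebo-controlled superiority trial takes the arm difference as the effect of adding the product to background therapy. Here both arms receive the product, in a ratio of ten to one, so the difference measures something narrower.

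The protocol does not treat the product as negligible. The Background and Discussion credit it with anti-inflammatory and immunomodulatory action, and the Interventions section bars other botanical medicines with such effects.

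Three readings are at stake:

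- **Efficacy.** A null DAS28 result would be taken as no benefit over background therapy, which this contrast cannot show.
- **Safety.** Safety is a stated aim. Similar adverse-event rates would be taken as no added harm from the product, yet no arm is unexposed. Dilution here flatters the product, so this is the more serious of the three.
- **Biomarkers.** The cytokine and protein comparisons planned in Table 3 and the Discussion use the same exposed control.

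**Working it through.** **1. Exposure in each arm.** The 17 original dosages in Table 2 sum to 2323.11 g per 1000 g of granule.

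- Per 12 g: 2323.11 × 12/1000 = 27.88 g. Per day (36 g): 2323.11 × 36/1000 = 83.63 g. Both reproduce the figures in the Interventions section.
- Control arm, at one tenth: 8.36 g per day.

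**2. What the arm difference estimates.** Let Δ be the effect of the full dose against no Wangbi, and f the fraction of that effect kept at one tenth of the dose. Then

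expected arm difference = Δ − fΔ = (1 − f)Δ.

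- With f = 0 nothing is lost. With f between 0 and 1 the difference understates Δ.
- If the product has no effect at any dose, both arms have the same expectation, so the type I error of the superiority test is unaffected.
- The same expression holds for adverse events, possibly with a different f. The article gives no dose response for either.

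**3. The plan's sample size.** The inputs in Sample size calculation are a difference of 0.5, one-sided α of 0.025, power of 80% (β of 0.2) and equal allocation; the stated result is 155 per group. No SD is stated, so 155 cannot be reproduced independently. Solving n = 2σ²(1.960 + 0.842)²/δ² for σ gives

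σ = 0.5/2.802 × √(155/2) ≈ 1.57.

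Other SDs give other sizes for δ = 0.5: 63 per group at SD 1.0, 124 at 1.4, 161 at 1.6.

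**4. Power, under two readings of the 0.5.**

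*Reading A: 0.5 is the difference between these two arms.* Nothing changes: 155 per group, 80% power.

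*Reading B: 0.5 is the effect against no Wangbi.* With σ = 1.571 and n = 155, the standard error is 1.571 × √(2/155) = 0.1785, and power = Φ(δ/0.1785 − 1.960):

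| f (assumed) | Arm difference | Power at 155 per group |
|---|---|---|
| 0 | 0.50 | 80% |
| 2% | 0.49 | 78% |
| 5% | 0.475 | 76% |
| 10% (linear dose response) | 0.45 | 71% |
| 20% | 0.40 | 61% |
| 30% | 0.35 | 50% |

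These figures depend as much on the unstated SD. At a difference of 0.45 and SD 1.4, the standard error is 1.4 × √(2/155) = 0.1590, and power is Φ(2.830 − 1.960), about 81%.

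**The case against.** The case for leaving the text alone has four parts.

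- **The composition is disclosed.** The Interventions section states it openly, and the article never calls the control inert. This is true. But the disclosure stays in the manufacturing paragraph and does not reach the sections where the contrast is named and the conclusions are drawn.
- **The formulation has a masking purpose.** It sits beside the matching of appearance and odour, and nothing here argues against it.
- **The bias is conservative for efficacy.** This stands if the small dose acts in the same direction. A positive superiority result remains valid for full against one-tenth dose. The argument does not carry over to safety, where moving toward no difference is not conservative. A tenfold exposure contrast does remain, so the safety comparison is weakened rather than empty.
- **The sample size is not shown to be wrong.** This stands. A reader might infer that the trial was powered as if the control were inert and really has about 71% power. The documents do not support that. The 0.5 is worded as the required difference between the intervention and control groups of this trial. The earlier studies are only referred to: the text does not say whether they supplied the difference, the SD or both, nor what their comparator was. The 71% needs three assumptions: a source contrast against no Wangbi, a linear dose response, and a back-solved SD.

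**Conclusion.** The point holds as one about the contrast and what may be concluded from it. The trial estimates full against one-tenth dose, while the design label, the expected conclusion and the limitations read as an ordinary placebo comparison.

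That the randomised contrast is full against one-tenth dose follows from the article alone. That differences against no Wangbi are understated rests on one assumption, that one tenth of the dose acts in the same direction as the full dose. How much they are understated cannot be derived from the article.

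A null efficacy result, or similar adverse-event rates, therefore could not be read as no effect or no added harm against no exposure. A positive superiority result is not undermined.

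No loss of power is established. The stated 80% stands if 0.5 already refers to these two arms. The 71% at a difference of 0.45 only illustrates the other reading. The article should say which reading applies.

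**What to change.** Leave the formulation as it is and change the text:

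1. Describe the comparator as a one-tenth-dose control wherever it defines the contrast: the Abstract's methods paragraph, Study design, Statistical analysis and Conclusion.
2. State once, plainly, that efficacy, safety and biomarker differences are full against one-tenth dose on background methotrexate and tofacitinib.
3. Qualify the Expected outcomes statement in the Abstract accordingly.
4. Add to the limitations in the Discussion that neither arm is unexposed, so a null efficacy result or similar adverse-event rates do not show absence of effect or harm against no exposure.
5. In Sample size calculation, say which contrast the 0.5 refers to and give the SD used. If it is the difference between these two arms, keep the 80%. Only if it was taken against no Wangbi should power be restated, for a smaller difference the authors can justify. The 71% above should not be written in as a finding.

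The cost is wording, plus a less favourable stated power if the second reading in item 5 applies. Supply, masking, visits and patients are unaffected.
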